### Interim analyses {21b}

Adverse events and clinically significant deterioration will be monitored, discussed, and reported. The lead statisticians will look for clinically significant deterioration on any outcome at the midpoint of the trials. Clinically significant deterioration will be determined through RCI analyses from baseline to the immediate post-treatment. If clinically significant deterioration is detected, a standardized procedure will follow.

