### Criteria for discontinuing or modifying allocated interventions {11b}

Individual withdrawal criteria will include the participant’s right to withdraw consent at any time without any negative consequences for their subsequent medical care. Participants may choose to withdraw if they experience adverse events or if they feel uncomfortable continuing in the study for any reason. Additionally, any significant changes in their medical condition that may affect their safety or the validity of the trial, such as newly diagnosed medical conditions or complications related to the surgical procedure, may also warrant withdrawal from the study. The research team will ensure that participants are fully informed of their right to discontinue their participation at any point during the trial, and efforts will be made to document the reasons for withdrawal if disclosed.

Withdrawal criteria for the overall PPULS trial may arise from significant changes in the safety landscape during the study period, such as emerging data that indicate an unacceptable level of risk for participants. This could include new findings related to the incidence of adverse events associated with the pneumoperitoneum pressures being tested, or if there are changes in clinical guidelines that recommend against the studied interventions. This trial will be discontinued only for reasons pertaining to efficacy, safety, or feasibility. However, at this stage, no specific overall withdrawal criteria have been identified; the study is designed with appropriate monitoring and safety protocols in place to ensure participant welfare throughout its duration.

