### Outcomes {12}

#### Primary outcome

The primary study endpoint is intraoperative blood loss in milliliters measured during the parenchymal transection phase. It will be referred to as *intraoperative blood loss during the parenchymal transection phase*.

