#### Secondary outcomes

The secondary endpoints of the study are defined as follows:Intraoperative blood loss in milliliters measured during the overall surgical procedure (from first skin incision to full skin closure)Incidence of CO_2_ embolisms in the right atrioventricular system detected by intraoperative transesophageal echocardiography with a mid-esophageal right ventricular inflow-outflow (RVOT) view before, during, and after the parenchymal transection phase. The occurrence of CO_2_ embolisms will be graded according to the “Tübingen Venous Air Embolism Grading Scale” [15]Other surgery-related secondary endpoints include:The quality of the surgical field (L-SRS)The overall time of surgery and the duration of the parenchymal transection phase in minutesIIP at the end of the parenchymal transection phase and mean IIP outside of the parenchymal transection phase, number of surgeries with an increase of +2 mmHg, +4 mmHg, or +6 mmHg, etc.Occurrence of intraoperative surgical complications other than gas embolismConversion rate to open laparotomyDifficulty of liver resection according to the “scoring system for laparoscopic liver resection”Indocyanine green (ICG) clearance after the parenchymal transection phase and 24 h laterOther anesthesia-related secondary outcomes include:Application of perioperative peridural catheter (drug, dosage, duration)Mean dose of narcotic drugs (propofol, sufentanil, remifentanil, lidocaine, esketamine, rocuronium, cisatracurium, and others)Transfusion rate and coagulation factor administrationNeuromuscular blockade reversal (sugammadex and others)Usage of vasopressors (epinephrine, noradrenaline, dobutamine, theodrenaline-cafedrine, and others)Use of buffer solutions (natrium bicarbonate and tris(hydroxymethyl)aminomethane)Mean EtCO_2_ and occurrence of an abrupt end-tidal carbon dioxide (EtCO_2_) partial pressure decrease ≥5 mmHg and mean arterial carbon dioxide pressure (paCO_2_), pH and bicarbonate at 15-min intervals during the parenchymal transection phase and every 30 min outside of itA sudden decrease in MAP > 20 mmHgAbnormal regional cerebral oxygen saturation (rScO_2_) (defined as a decrease in rScO_2_ > 15% compared with baseline or rScO_2_ < 50%)Mean central venous pressure (CVP) and increased CVP (CVP > 10) at 15-min intervalsPeripheral oxygen saturation (SpO_2_) <90%, or changes in SpO_2_ or hypoxia (SpO_2_ < 90% lasting at least 1 min)Heart rate (HR)Mean arterial pressure (MAP) and hypotension (MAP < 65 mmHg)Arterial lactateVentilation parameters: mean positive end expiratory pressure (PEEP), inspiratory pressure (Pinsp), mean airway pressure (Pmean), breathing ratePerioperative fluid balancePostoperative secondary outcomes include:Surgery-related postoperative complications (e.g., wound impairments, biliary leakage, postoperative liver failure, pulmonary complications)Overall postoperative morbidity within 30 postoperative days measured via the Comprehensive Complication Index (CCI) [16] according to the Clavien-Dindo classification [17]Dose of postoperative opioid analgesics (piritramide and others) and dose of postoperative non-opioid analgesics (metamizole, paracetamol, and others) for 48 h after the surgeryPostoperative laboratory values (e.g., bilirubin, c-reactive protein (CRP), international normalized ratio (INR))Length of the intensive care unit (ICU) stays, readmissions to the ICU, and overall hospital stayNausea and vomiting, use of emetic medications, day of first postoperative bowel movement, use of prokinetic medicationsQuality of recovery based on the Quality of Recovery 40 (QoR-40) questionnaire on postoperative days 1, 3, and 7Histopathology outcomes (e.g., lymph node yield, perineural and lymphovascular invasion)Postoperative neurological recovery according to the National Institutes of Health Stroke Scale (NIHSS)Outcomes assessed during follow-up include:30-day and 90-day survival.Hospital readmission within 30 days of remission.In case of a malignant diagnosis, oncologic outcome (overall survival and disease-free survival) will be evaluated based on [18] surgical margins (R0—no evident tumor along the transection surface or within 1 mm of it; R1—microscopically positive; R2—grossly positive).To assess the effect of pneumoperitoneum pressure on tissue damage:Plasma damage-associated molecular patterns (DAMPs), for example, heat shock protein 70 (HSP70), high mobility group box 1 (HMGB1), nuclear deoxyribonucleic acid (nDNA), and mitochondrial DNA (mtDNA).Plasma cytokines (for example, tumor necrosis factor alpha (TNFα), interleukin-10 (IL-10), and IL-6) will be evaluated from blood samples drawn directly before the parenchymal phase and at the end of it, as well as on postoperative days 1 and 3.In addition, liver and peritoneal biopsies will be taken before and after the parenchymal transection phase of the liver resection. Biopsies will be used to extract mRNA and determine:Levels of hypoxia-inducible factor 1-alpha (HIF1α), TNFα, IL-1β, IL-6, vascular endothelial growth factor (VEGF), hepatocyte growth factor (HGF), and platelet-derived growth factor (PDGF).

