## Data collection and management

### Plans for assessment and collection of outcomes {18a}

An outline of the study visits and a description of assessments are shown in Table 1.

**Table 1 Tab1:** Description of the time points and assessments of the study visits

Visit	Day	Description of assessments
Phase I: screening and inclusion in the study (intervention and control groups)		
V1	Outpatient clinic	- Inclusion/exclusion criteria - Informed consent - Assessment of sociodemographic data and medical history (*CRF 1*)
Phase II: intervention		
V2	Day of surgery	- Randomization to intervention/control group - Assessment of the surgical procedure (*CRF 2*) - Assessment of the anesthesia (*CRF 2*) - Collection of blood samples and peritoneal tissue samples at the beginning and the end of the parenchymal transection phase - Sampling of liver tissue from the liver resection specimen
Phase III: rehabilitation		
V3	POD 1	- Assessment of QoR-40 - Blood sampling
V4	POD 3	- Assessment of QoR-40 - Blood sampling
V5	POD 7	- Assessment of QoR-40
V6	Discharge from hospital	- Assessment of postoperative recovery (*CRF 3*)
Phase IV: follow-up		
V7	Follow-up at 3 months	- Telephone interview to assess outpatient rehabilitation (*CRF 4*)

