## Abbreviations

AEs: Adverse events
AS: American Society of Anesthesiologists (score)
BDSG: Bundesdatenschutzgesetz
CO_2_: Carbon dioxide
CI: Confidence interval
CONSORT: Consolidated Standards of Reporting Trials
CRF: Case report form
COPD: Chronic obstructive pulmonary disease
CVP: Central venous pressure
DAMPs: Damage-associated molecular patterns
DMC: Data Monitoring Committee
GDPR: General Data Protection Regulation
HGF: Hepatocyte growth factor
HIF1: Hypoxia-inducible factor 1 (alpha)
HPP: High-pressure pneumoperitoneum
HMGB1: High mobility group box 1
HSP70: Heat shock protein 70
ICC: Intra-class correlation coefficient
ICG: Indocyanine green
IIP: Intraperitoneal insufflation pressure
IL-1: Interleukin-1
IL-6: Interleukin-6
IL-10: Interleukin-10
L-SRS: Leiden Surgical Rating Scale
LPP: Low-pressure pneumoperitoneum
LDSG: Landesdatenschutzgesetz
MILR: Minimally invasive liver resection (or surgery)
mITT: Modified intention-to-treat
MAP: Mean arterial pressure
nDNA: Nuclear deoxyribonucleic acid
mtDNA: Mitochondrial DNA
NYHA: New York Heart Association
PFO: Patent foramen ovale
PDGF: Platelet-derived growth factor
PEEP: Positive end expiratory pressure
Pinsp: Inspiratory pressure
Pmean: Mean airway pressure
POD: Postoperative day
PPULS: Pneumoperitoneum PressUre for parenchymal transection in minimally invasive major Liver Surgery
QoR-40: Quality of Recovery 40
REDCap: Research Electronic Data Capture
rScO_2_: Regional cerebral oxygen saturation
RVOT: Right ventricular outflow tract
SD: Standard deviation
SOPs: Standard operating procedures
SpO_2_: Peripheral oxygen saturation
TNF: Tumor necrosis factor
TOF: Train-of-four
VEGF: Vascular endothelial growth factor
ICU: Intensive care unit
RCI: Reliable change index
NCT: Clinical trial identifier (as used in clinicaltrials.gov)

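### The criterion fixed for the midpoint look, a reliable change index from baseline, does not fit the trial's main harm outcomes and does not compare the arms

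*Protocol article*

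**What the plan says.** The Interim analyses section {21b} first says that adverse events and deterioration will be monitored and reported. It then schedules one look: "The lead statisticians will look for clinically significant deterioration on any outcome at the midpoint of the trials". The criterion is "Clinically significant deterioration will be determined through RCI analyses from baseline to the immediate post-treatment", and the abbreviation list gives "RCI: Reliable change index". The response to a signal is "If clinically significant deterioration is detected, a standardized procedure will follow".

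The section on discontinuing or modifying interventions {11b} names efficacy, safety and feasibility as grounds for ending the trial, and adds that "no specific overall withdrawal criteria have been identified".

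On the outcomes themselves:
- "The primary study endpoint is intraoperative blood loss in milliliters measured during the parenchymal transection phase".
- Embolism is graded by echocardiography in a "mid-esophageal right ventricular inflow-outflow (RVOT) view before, during, and after the parenchymal transection phase".
- The complication index covers the 30 days after surgery, and survival is assessed at 30 and 90 days.
- QoR-40 is listed for postoperative days 1, 3 and 7.
- Apart from eligibility and consent, the screening visit in Table 1 lists only "Assessment of sociodemographic data and medical history".

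**The concern.** A reliable change index asks whether one patient's score has moved by more than measurement error between two occasions. It needs the same scale measured before and after, and a reliability coefficient for that scale. It suits a symptom or function scale given before and after treatment. This trial's main outcomes are volumes lost and events that occur during or after one operation.

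The protocol expects opposing harms: more gas embolism at high pressure and possibly more bleeding at low pressure. A midpoint look is useful only if it can set one arm against the other on these outcomes. The protocol names a method that does not do this, so the problem is a stated method that does not fit, rather than detail left for later.

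**Working it through.** **1. What the index needs.** RCI = (post score − baseline score) / (SD × √(2 × (1 − reliability))). Four inputs are required: a baseline score, a post score on the same scale, an SD and a reliability. The article gives no reliability and no cut-off.

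**2. The outcomes set against that need.**

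| Outcome | Baseline score? | Immediate post-treatment score? | Usable index? |
|---|---|---|---|
| Transection blood loss (primary) | No, arises during transection | Yes | No |
| Total blood loss | No | Yes | No |
| Transfusion, conversion | No, events | Yes | No |
| Complication index | No | No, runs to 30 days | No |
| Survival | No | No, 30 and 90 days | No |
| QoR-40 | None listed | First on day 1 | Not in the visible schedule |
| CO2 embolism | Pre-transection reading exists | Yes | Not meaningful: event grade, no reliability given |
| Plasma markers, monitor readings | Yes | Yes | Could be formed, but these are not the main harms |

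**3. What it would return where it can be formed.** Assumptions for illustration: the conventional cut-off of 1.96, independent patients, no true change, and a midpoint of 132 / 2 = 66 patients. Then 2.5% of patients per outcome are flagged as deteriorated by chance.
- Expected false flags: 66 × 0.025 = 1.65.
- Chance of at least one: 1 − 0.975^66 = 0.81.

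These flags carry no information on which pressure is harmful. Real change after a major liver resection, to be expected in both arms, would add more.

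**4. What a by-arm comparison would return.** Inputs: severe embolism of 67.1% and 40.8%, quoted in the article's Discussion from an earlier randomized trial, and 66 / 2 = 33 patients per arm.
- Difference: 0.671 − 0.408 = 0.263.
- Standard error: √(0.671 × 0.329 / 33 + 0.408 × 0.592 / 33) = 0.118.
- 95% CI: 0.263 ± 1.96 × 0.118, about 3 to 49 percentage points.

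For blood loss, with the SD of 184 ml from the Sample size section {14}, the standard error of the difference is 184 × √(2/33) = 45.3 ml. The 95% half-width is 1.96 × 45.3 = 89 ml, against a non-inferiority margin of 100 ml. Both estimates are imprecise, but they address the question.

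**5. Power of a fixed p-value boundary at those embolism rates.** Pooled rate: (0.671 + 0.408) / 2 = 0.5395. Standard error under no difference: √(2 × 0.5395 × 0.4605 / 33) = 0.1227. Normal approximation:
- Two-sided p<0.05: Φ((0.263 − 1.960 × 0.1227) / 0.1184) = 58%.
- Two-sided p<0.001: Φ((0.263 − 3.291 × 0.1227) / 0.1184) = 12%.

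Exact calculation at p<0.001 gives 11% for the chi-squared test and 7% for Fisher's test. A very strict boundary would usually miss a difference of the size quoted.

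**6. The plan's own figure.** The interim section states no number to reproduce. The sample size, which supplies the 66 and 33 used here, does reproduce: 42 per group; × (1 + (42/4 − 1) × 0.05) = × 1.475 gives 62; / 0.95 gives 66 per group. The point does not depend on it.

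**The case against.** The strongest reply is that the index is not the only safeguard. The same section provides for adverse event monitoring, serious adverse events reach the principal investigator within 24 h, an independent DMC meets monthly, and unblinding is allowed for severe embolism. This stands. A reader might infer that the trial cannot detect its harms at all, and the documents do not support that. They support only that the midpoint look, under its stated criterion, cannot.

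Four further readings go too far:
- **Embolism has no baseline.** It has a pre-transection reading. The valid objection is that an index of measurement error on an event grade is not meaningful.
- **QoR-40 certainly has no baseline.** The visible text lists none, but the SPIRIT schedule (Fig. 2) is not shown and could contain one.
- **The look unblinds the statisticians.** The section does not say that the look is by arm or unblinded, and a within-patient index needs no arm labels.
- **Missing boundaries and interim alpha are errors.** These may sit in an analysis plan or DMC charter that is not shown. Efficacy appears in section {11b} only as one of three general grounds, and no interim efficacy test is described.

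It is also fair to say that the embolism rates come from a trial with 93.6% minor resections, so applying them here is an assumption. Finally, the defect leaves the primary estimate, the sample size and the non-inferiority conclusion untouched.

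**Conclusion.** The point holds in its narrow form. The stated criterion cannot be formed for blood loss, transfusion, conversion, complications or survival. It cannot be formed for QoR-40 on the visible schedule, and it is not meaningful for embolism. Where it can be formed, it does not compare arms. Followed as written, the midpoint look gives no usable result on the harms the trial expects.

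The mismatch rests on the outcome definitions alone. The illustrative figures rest on a midpoint at 66 patients split equally, a 1.96 cut-off with independent patients, and embolism rates carried over from the earlier trial. The paragraph should be corrected before the midpoint is reached.

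**What to change.** Replace the RCI sentence in section {21b} with wording to this effect: at the midpoint (about 66 patients), the independent DMC reviews by arm severe CO2 embolism, transection and total blood loss, transfusion, conversion, complications, serious adverse events and deaths. Between-arm differences are reported with confidence intervals and judged against a harm threshold that the DMC sets in advance. The look is for harm only, so the final alpha is unchanged.

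Do not make p<0.001 the default threshold, given its power of about 12% in the example. Replace the undefined standardized procedure with the steps that follow a signal, or refer to the document that holds them. Reconcile the harm-only statement with the mention of efficacy in section {11b}.

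The cost is one paragraph and a matching edit in {11b}. The data are already collected and the DMC already meets monthly. The article estimates that recruitment will be complete by December 2027; the change should be in place before the look takes place.

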### Methods for additional analyses (e.g., subgroup analyses) {20b}

Not applicable as no subgroup analyses are planned.

### Methods in analysis to handle protocol non-adherence and any statistical methods to handle missing data {20c}

For the primary analysis, a complete-case analysis will be performed, considering only patients with complete data. Missing data will not be imputed unless the proportion of missing data is determined to be significant. Additionally, a multiple imputation method will be employed as a sensitivity analysis to assess the robustness of the results in the presence of missing data and to minimize potential bias from non-randomly missing values.

### Plans to give access to the full protocol, participant level data, and statistical code {31c}

The study protocol and any de-identified database or statistical code required to support the protocol will be supplied on request.

## Oversight and monitoring

### Coordinating center and trial steering committee {5d}

The trial’s day-to-day operations are managed by a coordinating center composed of qualified physicians, study nurses, and clinical scientists. This team is responsible for operational oversight, protocol adherence, and organizational support. A trial steering committee, comprising these same professionals, meets on a monthly basis to review progress and address any issues; meeting frequency can be increased as needed.

### Composition of the data monitoring committee, its role and reporting structure {21a}

An independent Data Monitoring Committee (DMC) is established to oversee participant safety and data integrity. This committee is similarly composed of physicians, study nurses, and clinical scientists ensuring that expertise is maintained across trial oversight functions. The DMC meets monthly, with the meeting interval shortened if required by emerging safety or efficacy concerns.

### Adverse event reporting and harms {22}

Participation may involve certain risks and burdens for the study participants. While the use of high pneumoperitoneum pressure (HPP) aims to reduce intraoperative blood loss and associated complications, there remains a potential risk of CO_2_ embolisms due to the insufflation of carbon dioxide. Additionally, the intraoperative monitoring techniques to detect CO_2_ embolisms, and transesophageal echocardiography, may introduce discomfort or risks typically associated with invasive procedures. Rarely, echocardiography causes arrhythmias, infections, or dental damage. Prolonged use of the echocardiography probe during intraoperative monitoring can result in minor injuries to the mucosal surface and hematomas in the esophagus. Very rarely, esophageal injuries that lead to perforation—especially in patients with preexisting esophageal conditions—can occur and may cause mediastinitis. Participants may also experience anxiety related to undergoing surgical procedures and being part of a clinical trial. Moreover, while efforts will be made to minimize postoperative complications, there is still a possibility of adverse outcomes, such as prolonged recovery or the need for additional interventions. However, it is essential to note that the study protocol has been designed to adhere to strict ethical guidelines, and any risks will be communicated to participants during the informed consent process. Overall, the research team will continuously monitor participant safety throughout the study to mitigate these risks as effectively as possible.

“Adverse events” (AEs) will be recorded on a special AE form in the CRF. AEs will be reported to the principal investigator at regular intervals throughout the study. “Serious adverse events” (SAEs) that result in death, are life threatening, require hospital admission, result in persistent or significant disability or incapacity, or result in reoperation due to any reason will be documented on a special SAEs formula in the CRF and will be reported to the principal investigator within 24 h.

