## Statistical methods

### Statistical methods for primary and secondary outcomes {20a}

The data will be managed and analyzed according to the applicable standard operating procedures (SOPs) within the shared unit of the clinical trial center. All relevant study information will be documented in case report forms (CRFs), which will be reviewed by the study team prior to data entry. A safety analysis will be conducted for all patients who underwent one of the interventions. Serious adverse events will be documented immediately, prompting notification of the principal investigator. Absolute and relative frequencies, as well as the severity and relationship to the intervention, will be compared between intervention groups.

The modified intention-to-treat (mITT) analysis will be used to evaluate the primary and secondary endpoints. The mITT set includes all randomized patients who initiated the intervention and met intraoperative inclusion criteria (e.g., exclusion of a PFO). Patients excluded intraoperatively due to contraindications (e.g., adhesions or peritoneal carcinomatosis) will not be included in the analysis.

The primary endpoint (intraoperative blood loss during the parenchymal transection phase) will be analyzed using linear regression if data follow a normal distribution. If normality is not met, a non-parametric bootstrap method will be employed to calculate confidence intervals. The 90% confidence interval (CI) for the mean difference between the two groups will be calculated, and the lower bound of this interval will be compared to the predefined non-inferiority margin of 100 ml to confirm non-inferiority. The corresponding *p* value will also be computed.

Secondary endpoints will also be analyzed:Continuous variables: These will be analyzed using descriptive statistics (mean, standard deviation, quartiles) along with two-sided 95% confidence intervals (CIs).Categorical variables: Absolute and relative frequencies will be reported, and two-sided *p* values will be calculated using the chi-squared test or Fisher’s exact test.

All statistical tests will be two-sided and conducted at a significance level of *α* = 0.05. Analyses will account for stratification to minimize bias and ensure accurate *p* values [22].

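### The SAE definition has no criterion for prolonging an existing hospital stay, so some in-hospital complications lack SAE status and 24-hour reporting that they would have after discharge

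*Protocol article*

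**What the plan says.** The section Adverse event reporting and harms {22} gives an explicit list of seriousness criteria. An event is serious if it is among those "that result in death, are life threatening, require hospital admission, result in persistent or significant disability or incapacity, or result in reoperation". The last criterion is broad, since it reads "or result in reoperation due to any reason".

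The same section sets two reporting speeds. Serious events "will be reported to the principal investigator within 24 h". For the rest, "AEs will be reported to the principal investigator at regular intervals throughout the study", and no interval is given.

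Statistical methods {20a} adds that "Serious adverse events will be documented immediately, prompting notification of the principal investigator". This concerns timing and does not widen the definition. The paragraph ends: "Absolute and relative frequencies, as well as the severity and relationship to the intervention, will be compared between intervention groups".

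Table 1 places surgery at V2, hospital discharge at V6 and one later contact, V7, at 3 months. The secondary outcomes include "Surgery-related postoperative complications (e.g., wound impairments, biliary leakage, postoperative liver failure, pulmonary complications"), 30-day morbidity on the Comprehensive Complication Index, ICU stay, ICU readmission, total hospital stay and 30-day hospital readmission.

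**The concern.** Hospitalisation enters the definition only as a new admission. In a trial of elective liver surgery every participant is already in hospital when the intervention is delivered and stays there until V6. A criterion that depends on being admitted does little in that period, and nothing in the list takes its place.

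The section itself names harms "such as prolonged recovery or the need for additional interventions" as possible. Neither makes an event serious under the list, unless the additional intervention is a reoperation or another criterion is met.

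Two things are at stake. The first is speed, because the 24-hour route is open only to events classed as serious. The second is consistency, because the same complication is classed differently according to whether the patient has gone home.

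**Working it through.** No arithmetic applies. The question is whether each listed criterion can be met by a patient who is already in hospital, and whether any other text fills a gap.

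**Step 1: the criteria, one by one ({22}).**

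| Criterion | Can it be met between V2 and V6? |
|---|---|
| Death | Yes |
| Life threatening | Yes |
| Hospital admission needed | Not ordinarily; the patient is already admitted |
| Persistent or significant disability or incapacity | Yes |
| Reoperation for any reason | Yes |

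Four of the five criteria work before discharge and one does not.

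**Step 2: other text.** The sentence on serious events in {20a} sets immediate documentation and notification but gives no criterion. The secondary outcomes record ICU readmission and length of stay as outcomes, not as triggers for seriousness. No other section of the article defines a serious event or mentions prolongation of a stay as a criterion.

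**Step 3: what falls through.** The residual group is the in-hospital event that lengthens the stay and is not fatal, not life threatening, not disabling and not followed by reoperation. Two examples are a biliary leak managed without reoperation and an ICU readmission that is not life threatening.

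**Step 4: the same event on either side of discharge.**

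- Bile leak before V6, managed without reoperation, stay lengthened: no criterion met. It is an adverse event, reported at regular intervals.
- Bile leak after V6, managed without reoperation, patient readmitted: admission criterion met. It is a serious adverse event, reported within 24 hours.

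The event is the same. Only the patient's location differs.

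**Step 5: what is kept.** The event before V6 is still entered on the adverse event form. Biliary leakage is named among the postoperative complications collected as secondary outcomes. A surgical complication within 30 days also enters the morbidity index, and the longer stay or ICU readmission is recorded in its own right. The data are therefore not lost; the SAE label and the fast route are.

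**The case against.** The strongest reply is that the gap is small and well covered. In-hospital deaths, life-threatening embolism or bleeding, disabling sequelae and every reoperation still reach the principal investigator within 24 hours. A reader might infer that serious complications before discharge in general escape expedited reporting. The list does not support that, and the point is confined to the residual group described above.

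A reader might also infer that the trial under-counts in-hospital harm. The documents do not support this either, because complications, morbidity, ICU readmission and stay are collected whatever the SAE status.

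A third inference is bias between arms: the Discussion cites a shorter stay with low pressure in colorectal surgery, so one arm might become eligible for admission-type events sooner. This is conjecture. The cited stay comes from a different operation, and the article gives no expected stay for this trial. The comparison sentence in {20a} is not limited to serious events. Any shift could also be examined, since hospital stay and 30-day readmission are both outcomes.

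Other oversight also counts. The data monitoring committee meets monthly, or sooner if concerns emerge, and {21b} provides for monitoring of adverse events and a midpoint check for deterioration. These arrangements limit the consequence but do not replace a 24-hour route.

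Finally, it could be said that an article condenses the full protocol. That would answer a missing definition. Here the article states the definition criterion by criterion, so the finding rests on what it says.

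**Conclusion.** The point holds in a limited form. The stated definition lacks a criterion for prolonging an existing hospital stay. In-hospital complications that lengthen the stay but meet none of the other four criteria are not classed as serious and are not reported within 24 hours, whereas the same event leading to readmission would be. The loss is of SAE status and expedited reporting, not of documentation.

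Its size in events cannot be given. The article states no rate for complications that lengthen the stay, and no share of them that would meet another criterion, so any count would rest on outside assumptions. That such complications arise largely before discharge is a reasonable inference from the visit schedule and the listed complications, but the article gives no figure for it.

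The conclusion assumes that the admission criterion is read literally and that the article reproduces the operative definition. The primary endpoint, the sample size and the non-inferiority test are not affected. This is a cheap improvement to safety reporting.

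**What to change.** In {22} and on the SAE form, change the hospitalisation criterion to *require hospital admission or prolong an existing hospital stay*, and leave the other four criteria as they are. If the full protocol already contains this criterion, correct the article to match it. No change to the reporting period is needed, since no fault was found there.

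The cost is one phrase in the protocol and on the form, and somewhat more SAE forms to complete. ICU readmission and hospital stay are already collected, so no new data items are required. The change concerns the reporting definition only and alters no treatment.
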